### Data collection, management and analysis

#### Data collection methods

Participants will give fasted blood samples and undergo anthropometric measurements at three timepoints, baseline, 6 weeks and 12 weeks. All the clinical data (metabolic syndrome risk factors) will be recorded in clinical research files. As detailed in the data management plan below, these will be scanned and copies saved electronically as well as in physical format. At each visit, participants will be asked to complete a brief online health questionnaire and an online food frequency questionnaire (FFQ) adapted from our validated short (45-item) FFQ [29] to include food items rich in ergothioneine.

#### Blood sample collection

Minimal amounts of blood will be taken from participants to limit the burden of bleeding. At three timepoints: baseline (before starting capsule supplementation), 6 weeks follow-up and end of the study, we will ask to take a finger prick blood sample to measure participants blood TAG, HDL cholesterol, fasting glucose and CRP. In addition, participants will be asked to provide 15 ml of blood sample for measurement of platelet function, inflammatory biomarkers and metabolites. Fifteen milliliters of blood donation is safe for adults and venepuncture will be done by a trained phlebotomist to ensure that distress during blood collection will be minimal and that correct procedures for collection, processing and storage are followed. Five milliliters of whole blood will be immediately used for platelet function assays using multicolour flow cytometry assessment of surface markers of platelet activation, platelets subsets, platelet ROS generation and platelet-leukocyte aggregates [30]. Platelet function will be addressed under basal conditions in order to evaluate activation status of circulating platelets and after stimulation with known agonists to examine if their propensity for activation is altered. The remaining 10 ml will be centrifuged for the collection of acellular serum, aliquoted and stored at − 80 °C for future laboratory analysis. Stored serum will be compliant (i.e. exempt from regulation) with the 2004 Human Tissue Act.

#### Metabolic syndrome risk factors

Height will be measured with a stadiometer at baseline. Bodyweight, blood pressure, waist circumference will be measured with a beam scale, blood pressure monitor and tape respectively at baseline, 6 weeks and 12 weeks. TAG, HDL-C and fasting glucose will be measured in whole blood using a rapid point-of-care multi-assay blood analyser (Afinion 2 analyser; Abbott, UK) at baseline, 6 weeks and 12 weeks.

#### Biomarkers assessment

CRP will also be measured from a finger prick of whole blood by a rapid point-of-care multi-assay blood analyser. MDA will be measured in purified serum samples by HPLC. The TNF-α and Nrf2 proteins will be measured in purified serum samples using enzyme-linked immunosorbent assay (ELISA) kits. NOX4 mRNA expression will be measured in purified serum samples by quantitative polymerase chain reaction. ALT activity will be measured in serum samples using a commercial assay kit.

#### Metabolite assessment

 Ergothioneine and its metabolites (hercynine, ergothioneine sulfonate and *S*-methyl ergothioneine), as well as other metabolites will be measured in serum by liquid chromatography-mass spectrometry (LC-MS).

#### Online questionnaires

Online health questionnaire and FFQs will be used to record the health condition, dietary habit and quality at baseline (visit 1), 6 weeks (visit 2) and end of the study (12 weeks, visit 3).

### Data management, confidentiality and access

All data will be managed through a Microsoft Access database with data entered using encrypted, two-factor authentication protected, computers owned by the University of Leeds. Electronic data will be stored on the University of Leeds SAN (Storage Area Network), which comprises enterprise level disk storage and file servers located in physically secure data centres with appropriate fire suppression equipment and daily/monthly/long-term back up protocols. The SAN is located behind the University’s Institutional firewall to protect against external attacks.

Physical format clinical research files (used to collect clinical data during visits; template available in appendix of our approved ethics application) will be scanned and copies saved electronically as well as in physical format in locked cabinet in the chief investigator’s secure office. Data entry from clinical research files will be confirmed independently by second investigator. Questionnaires (primary eligibility screening questionnaire, health questionnaires, FFQs) will be collected in a digital format.

Data will be collected anonymised with only participants’ randomisation number and date of birth recorded on the data collection tools. Anonymised data will be shared, published and used in line with the University of Leeds Research Data Management Policy. Any personal details, identifiable or sensitive information will not appear in any publications. The data will be retained for at least 2 years after publication. Only research team members will have access to the data.

### Statistical methods

Descriptive statistics will be used initially to present the basic features of the data, with data presented as mean/SD or percentage used as appropriate in response to normality testing using (Table 2). Linear regression and two-way ANOVA will be performed to analyse the associations between variables (Table 3). The significance level will be set at 5% and 95% confidence intervals will be presented. Intention-to-treat analysis will be performed to compare the difference with per-protocol analysis. Basic analyses will be performed in GraphPad Prism. Multivariate linear regression will be done either in STATA or the R environment in consultation with statistician/mathematical modeller as required.

**Table 2 Tab2:** Descriptive characteristics

	Mean ± SD or %
Age (years)	
Ethnicity	
Asian/Asian British	
White and all other ethnic groups	
Sex	
Male	
Female	
Smokers	
Alcohol intake (units/week)

**Table 3 Tab3:** ErgMS measurements and schedule

Measurement	Study visit		
	Baseline	6 wks	12 wks
Primary			
Recruitment			
Completion			
Supplementation compliance			
Secondary			
Platelet function			
MDA			
ALT			
TNF-α			
Nrf2			
CRP			
Fasting glucose			
TAG			
HDL-C			
Weight			
BMI			
WC			
Systolic BP			
Diastolic BP			

*ALT* Alanine transaminase, *BMI* Body mass index, *BP* Blood pressure, *CRP* C-reactive protein, *HDL*-*C* High-density lipoprotein-cholesterol, *MDA* Malondialdehyde, *Nrf2* Nuclear factor erythroid 2-related factor 2, *TAG* Triacylglyceride, *TNF*-*α* Tumour necrosis factor-alpha, *WC* Waist circumference, *wks* Weeks

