**Methods:**

We have designed the ErgMS study as a single-centre, randomised, double-blind, placebo-controlled, 3-arm parallel, pilot intervention trial, which aims to supplement participants with either placebo, 5 or 30 mg/day ergothioneine for 12 weeks. Measurements of metabolic syndrome risk factors, serum markers of oxidative stress (lipid peroxidation), inflammation, blood platelet function and liver function will take place at baseline, and after 6 weeks and 12 weeks of supplementation. In addition, we will examine if there are any changes in the serum metabolome in response to ergothioneine supplementation. Linear regression and two-way ANOVA will be utilised to analyse the association between ergothioneine and measured variables.

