### Interventions

Consenting participants will be randomised in a double-blind fashion to one of three intervention groups that will receive either placebo (0 mg ergothioneine), 5 mg ergothioneine or 30 mg ergothioneine for consumption as daily capsules (one per day) for 12 weeks (Fig. 1). Both placebo and ergothioneine supplement capsules will be manufactured by Tetrahedron (Paris, France). The placebo capsules will have the same shape, colour, weight and packaging as the ergothioneine capsules. Participants can withdraw from the study at any time if they want to withdraw without reasons by contacting the researcher. Data already collected from any withdrawals will be kept in the dataset and used in intention-to-treat analysis.

To promote adherence, participants will be sent periodic reminder/enquiry texts before each visit and will be informed of their clinical parameters at each visit and the final results after the trial data has been analysed and unblinded. Supplementation compliance will be measured both by capsule counting (participants will be asked to return package and untaken supplements at 6 weeks and 12 weeks) and the measurement of ergothioneine in plasma by high-performance liquid chromatography (HPLC) at baseline, 6 weeks and 12 weeks.

Related to the exclusion criteria, participants will be asked not to start taking dietary/antioxidant supplements, implement a new diet/fitness regime or take prescription anti-inflammatory medicines (occasional aspirin, paracetamol, ibuprofen use acceptable) for the duration of the trial.

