### Assignment of interventions

#### Allocation

While enrolment will be done by the study team, the randomisation schedule and allocation will be carried out by a collaborator who will not be involved in any other part of this trial and who will also be blinded to the dose allocation (Interventions ‘1’, ‘2’ or ‘3’; Fig. 1) designated by the manufacturer and provided in a sealed envelope. Randomisation and group allocation will be done based on predefined random allocation lists using simple stratification for sex (one each for males and females), with a block size of 6 and allocation list of 2:2:2; aiming to recruit 108 participants for *n* = 36 in each group.

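### The named two-way ANOVA leaves its factors and error term open, and on the arm-by-visit reading neither standard version suits three repeated visits with withdrawals; a baseline-adjusted mixed model would.

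*Protocol article*

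**What the plan says.** Statistical methods states: "Linear regression and two-way ANOVA will be performed to analyse the associations between variables (Table 3". The abstract has the same pair of methods: "Linear regression and two-way ANOVA will be utilised to analyse the association between ergothioneine and measured variables". Table 3 lists the measurements against three visit columns: baseline, 6 weeks and 12 weeks. Statistical methods adds "Multivariate linear regression will be done either in STATA or the R environment in consultation with statistician/mathematical modeller as required", without listing covariates, and "The significance level will be set at 5% and 95% confidence intervals will be presented". It plans both intention-to-treat and per-protocol analyses.

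On the design, Data collection methods says "Participants will give fasted blood samples and undergo anthropometric measurements at three timepoints, baseline, 6 weeks and 12 weeks". Blood sample collection makes clear that the first of these precedes treatment: "baseline (before starting capsule supplementation), 6 weeks follow-up and end of the study". There are three arms. Randomisation is stratified, "using simple stratification for sex (one each for males and females), with a block size of 6 and allocation list of 2:2:2", with 36 per arm. Sample size aims for 30 measured per arm and allows for 20% dropout. Interventions says of participants who leave: "Data already collected from any withdrawals will be kept in the dataset and used in intention-to-treat analysis".

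Recruitment, completion and compliance are the primary outcomes. All biomarkers are secondary and exploratory. MDA is put forward as a possible primary outcome for the later trial.

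**The concern.** The article commits to a method by name, in two places, for data with three correlated values per person. The name covers more than one analysis, and the text does not say which is meant. With three arms and a table whose columns are the visits, arm by visit is the natural reading. On that reading, no standard two-way ANOVA does all three things the design calls for: a correct error term for every test, baseline treated as a pre-treatment measurement rather than as a response, and use of the partial data of people who withdraw.

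The study exists to choose an outcome, a dose and a sample size for a definitive trial. What is at stake is the quality of the estimates it hands on, together with any 5% significance statements made along the way.

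**Working it through.** **Inputs from the article.** Three arms; 30 measured per arm (36 recruited); three visits; baseline before treatment; 5% level; 20% dropout.

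**Assumed, because the article gives no figures.** Within-person correlation ρ of 0.3 to 0.8, equal between all pairs of visits; normal outcomes with SD 1; treatment effects as stated below. The article has no power figure to reproduce.

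**1. Ordinary two-way ANOVA (all observations treated as independent).** The variance of a person's mean over three visits is (1 + 2ρ)/3, but the model assumes 1/3. The arm F is therefore inflated by 1 + 2ρ, and the interaction F is deflated by 1 − ρ. Simulated rejection under no effect, 30 per arm, complete data:

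| ρ | 1 + 2ρ | arm main effect | 1 − ρ | arm-by-visit |
|---|---|---|---|---|
| 0.3 | 1.6 | 15.9% | 0.7 | 0.9% |
| 0.5 | 2.0 | 21.8% | 0.5 | 0.1% |
| 0.7 | 2.4 | 28.7% | 0.3 | 0.0% |
| 0.8 | 2.6 | 31.2% | 0.2 | 0.0% |

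Two quantities are not harmed. A dose-minus-placebo contrast at week 12 compares different people, and its type I error is about 5% at every ρ. The residual SD averages 1.00 against a true value of 1.

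**2. Classical repeated-measures two-way ANOVA.** With complete data, both the arm and the interaction test reject 4.9% to 5.4% of the time under no effect, so the error term is right. But the method needs all three visits. At 20% dropout, 36 × 0.8 = 28.8 per arm remain. The 6-week values of people who leave before week 12 are discarded, although Interventions says collected data will be used.

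**3. Baseline as one of three visits.** A constant effect δ at weeks 6 and 12 gives an arm main effect of (0 + δ + δ)/3 = 2δ/3. The interaction does not have this dilution. Power for assumed effects of 0, 0.3 and 0.6 SD across the arms at both post-baseline visits, complete data:

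| ρ | repeated-measures arm effect | repeated-measures interaction | week-12 ANCOVA on baseline |
|---|---|---|---|
| 0.3 | 44% | 40% | 56% |
| 0.5 | 37% | 54% | 65% |
| 0.7 | 31% | 79% | 82% |
| 0.8 | 29% | 94% | 93% |

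ANCOVA's type I error was 4.8% to 5.3%. Its variance relative to the unadjusted week-12 comparison is 1 − ρ²: 0.91, 0.75 and 0.51 at ρ = 0.3, 0.5 and 0.7.

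**4. Sex.** A separate simulation had 30 per arm, balanced 15/15 within sex, and a single outcome without baseline. Omitting sex gave type I error of 4.3% for an assumed sex difference of 0.5 SD and 2.6% for 1.0 SD, against about 5% when adjusted. Power fell from 53% to 49% and from 51% to 39%. Omission is therefore conservative.

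**The case against.** The strongest reply is that the article never specifies the analysis criticised here. It names no factors, no error term and no role for baseline. That is correct: arm by visit is inferred from a table that is chiefly a measurement schedule. A reader might infer that the plan has simply chosen a wrong model. The text does not support this, and the two main problems belong to different versions. The ordinary ANOVA can use withdrawals' rows, and the repeated-measures ANOVA has the right error. They are not defects of a single analysis.

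A reader might also infer that the SDs and week-12 estimates passed to the later trial would be distorted. Even in the ordinary version they are not (step 1). The inflated error concerns only a main effect averaged over visits, which the article never names as its target. The repeated-measures interaction is a valid test and nearly matches ANCOVA at high correlation.

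Nor does the article exclude sex or baseline. Linear and multivariate regression are also planned and could carry both; the Discussion already foresees examining vaccination timing as a confounder. An article may leave covariate lists to a fuller document. Likewise, regression on ergothioneine may mean assigned dose rather than measured concentration.

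All of this stands and limits the point. It does not remove it. A method is named, its natural reading has no version that meets the whole design, and the undertaking on withdrawals is at odds with the version whose error term is right.

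**Conclusion.** The point holds as a moderate one. If the two-way ANOVA is arm by visit, either its arm main effect is anti-conservative (about 16% to 29% at ρ from 0.3 to 0.7) and its interaction test very conservative, or it drops about 7 of 36 per arm (36 − 28.8 = 7.2) and some data that the article says will be used. In both, an arm main effect is cut to two thirds. The valid repeated-measures interaction is less powerful than baseline-adjusted ANCOVA unless ρ is about 0.8. That no model names sex is a secondary matter, since omitting it makes tests mildly conservative.

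No confirmatory test depends on this. The harm is lost precision and unused data in the estimates meant to inform the definitive trial. Every error and power figure rests on assumed correlations, effects and sex differences; the factor of two thirds assumes an equal effect at weeks 6 and 12.

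**What to change.** Replace the two-way ANOVA in Statistical methods, and in the abstract, with wording such as:

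*Each continuous outcome will be analysed with a linear mixed model of the 6- and 12-week values. Fixed effects are arm, visit, arm-by-visit, baseline value, baseline-by-visit and sex; errors within a participant are correlated. The estimates are each dose minus placebo at week 12, with 95% confidence intervals, in all randomised participants with any post-baseline value.*

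Add a rule for participants with no post-baseline value, because this model does not use them and Interventions says collected data will be used. State whether regression on ergothioneine means assigned dose or measured concentration. If concentration, label it exploratory and non-randomised, since diet and adherence also affect it.

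The cost is a paragraph of wording. The model needs no further data and is routine in Stata or R, both of which the article already names.

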### Monitoring

The ErgMS trial management group will be comprised of the Chief ([name]) and lead investigators (XT, JS, JT) and will be responsible for the day-to-day running and management of the trial. As ergothioneine is an amino acid normally found in food and the doses of ergothioneine being tested (5 or 30 mg/day) are well below the safety limit (800 mg/kg bodyweight per day—e.g. a total of 56,000 mg/day for a 70 kg adult), the risk of harm or adverse event for adult participants with metabolic syndrome is considered low. Ergothioneine has minimal allergy risk determined by European Food Safety Authority [17]. Participants will be asked to inform the researcher if they feel unwell at any point during the study and their general health will be assessed through the health questionnaire at the 6- and 12-week visits.

Any participant reported adverse events will be recorded by the member of the trial management group in our adverse event reporting form and immediately report it to the Chief Investigator and assessed for causality. As necessary, the participant will be advised to consult their GP or relevant healthcare professional. In light of the relatively low risk study population with a noncritical indication (adults with metabolic syndrome), use of a food supplement with minimal risk, and short study duration, the ErgMS study does not have an independent data monitoring committee. In the unlikely event of a serious adverse event (SAE), the participant’s allocated intervention will be unblinded and the SAE and allocation will be reported to the Research Ethics Committee and the supplement manufacturer. Although there are minimal risks anticipated for this study, any adverse event or serious adverse event will be described according to its relatedness with the interventions, for both the total sample and by intervention arms, in the final study report.

### Protocol amendments

Any modifications of the protocol that may affect the conduct of the study, participant recruitment, the information provided to participants or the data analysis will be submitted to the University of Leeds Research Ethics Committee as an amendment and communicated to ISRCTN after approval. As necessary, any changes affecting participants currently enrolled will be communicated to participants after approval and being applied to the study.

### Dissemination plans

Regardless of the magnitude or direction of effect, the results will be disseminated in a timely fashion through presentation first at scientific conferences and then via publication in open access, peer-reviewed journals. In addition, progress reports and results will be available on the trial website and communicated via social media to a wider audience. The full protocol, and ultimately the anonymised dataset and any relevant statistical code, will be deposited in the Leeds Research Data Repository and available open access.

## Discussion

Ergothioneine is a dietary nutrient that is sold as a dietary supplement for its antioxidant and anti-inflammatory properties. However, to date, there are no published intervention trials examining its efficacy in humans. Therefore, along with examining feasibility, the ErgMS study aims to establish primary and secondary outcomes, and the power required, for a definitive randomised controlled trial to test the hypothesis that ergothioneine supplementation is beneficial for people with metabolic syndrome.

A significant body of preclinical data has demonstrated antioxidant and anti-inflammatory activities of ergothioneine that are relevant to the prevention of cardiometabolic diseases [4, 5]. These data underpinned our decision to first investigate ergothioneine in people with metabolic syndrome, who are at risk of developing diabetes and non-alcoholic fatty liver disease (NAFLD), as well as cardiovascular and atherothrombotic diseases [21]. Considered the hepatic manifestation of the metabolic syndrome [31], NAFLD involves chronic oxidative metabolism, lipid peroxidation and inflammation that can progress to liver fibrosis [32]. Interestingly, ergothioneine has been shown to be protective in both animal models of NAFLD [33] and liver fibrosis [34], informing our measurement of MDA, a primary serum marker of lipid peroxidation, as well as ALT, a marker of liver function in this study. Similarly, several of the inflammatory markers we intend to measure have been shown to be modulated in protective fashion by ergothioneine in preclinical models; e.g. TNF-α [35], Nrf2 [36] and NOX4 [34]. In the context of COVID-19, a possible factor affecting measures of inflammation might be vaccination timing, and this information will be collected from participants and examined as a potential confounder.

Alterations in platelet function, including platelet hyperaggregability and hyperactivation is commonly seen in people with metabolic syndrome and contributes fundamentally to the increased risk of atherothrombotic diseases [37, 38]. Oxidative stress plays a critical role in platelet hyperactivity, with platelet activation driven by ROS present both in the vasculature and generated by platelets themselves. Dietary antioxidant intakes are inversely associated with cardiovascular and atherothrombotic diseases [39], and multiple dietary supplements and nutraceuticals have been shown to impact platelet function [40–42]. Although the antioxidant activities of ergothioneine in scavenging hydroxyls and other free radicals is well documented [3], to date the role of ergothioneine in human platelet function has not been explored. Therefore in the ErgMS study, we will assess platelet function using multicolour flow cytometry to measure surface markers of platelet activation, platelets subsets, platelet ROS generation and platelet-leukocyte aggregates [30].

Potential limitations to this study exist, including the fact that there were no data on which to base the length of supplementation period for ergothioneine. Therefore, the decision to supplement for 12 weeks, with measurements also taken at 6 weeks was a pragmatic one. Although serum MDA has been shown to respond to intervention with other dietary supplements within 12 weeks [43, 44], these are not directly comparable to ergothioneine. Likewise, there were no data on which to base the dose of ergothioneine for supplementing people with metabolic syndrome, and pragmatically the decision was based to supplement with the amounts (5 mg and 30 mg) commonly available and well within the safety margins defined by EFSA [17]. In the only human study published to date, where healthy participants received either placebo, 5 or 25 mg ergothioneine/day for 7 days, a dose-dependent effect on levels of ergothioneine in plasma, urine and whole blood were observed [11]. However, data from mice orally administered either saline, 35 or 70 mg/kg ergothioneine per day for 1, 7 or 28 days, suggests saturation kinetics exist for ergothioneine uptake and accumulation in animal tissues [12]. Therefore, it is difficult to predict whether the lower or higher dose of ergothioneine may be more beneficial over 12 weeks for people with metabolic syndrome.

An additional potential implication from the ErgMS design is that while the exclusion criteria reflect our objective of focusing on metabolic syndrome and excluding other inflammatory conditions, the large number of exclusion criteria may result in a longer recruitment period. Nonetheless, the ErgMS study will be the first study to address the question does ergothioneine supplementation have health benefits for people with metabolic syndrome. Study results will provide novel, preliminary data as to which dose may improve inflammatory markers in adults with metabolic syndrome, and inform dose and primary outcome selection for a definitive RCT.

